## Abstract

**Background:**

This study seeks to extend earlier Australian school drug education research by developing and measuring the effectiveness of a comprehensive, evidence-based, harm reduction focused school drug education program for junior secondary students aged 13 to 15 years. The intervention draws on the recent literature as to the common elements in effective school curriculum. It seeks to incorporate the social influence of parents through home activities. It also emphasises the use of appropriate pedagogy in the delivery of classroom lessons.

**Methods/Design:**

A cluster randomised school drug education trial will be conducted with 1746 junior high school students in 21 Victorian secondary schools over a period of three years. Both the schools and students have actively consented to participate in the study. The education program comprises ten lessons in year eight (13-14 year olds) and eight in year nine (14-15 year olds) that address issues around the use of alcohol, tobacco, cannabis and other illicit drugs. Control students will receive the drug education normally provided in their schools. Students will be tested at baseline, at the end of each intervention year and also at the end of year ten. A self completion questionnaire will be used to collect information on knowledge, patterns and context of use, attitudes and harms experienced in relation to alcohol, tobacco, cannabis and other illicit drug use. Multi-level modelling will be the method of analysis because it can best accommodate hierarchically structured data. All analyses will be conducted on an Intent-to-Treat basis. In addition, focus groups will be conducted with teachers and students in five of the 14 intervention schools, subsequent to delivery of the year eight and nine programs. This will provide qualitative data about the effectiveness of the lessons and the relevance of the materials.

**Discussion:**

The benefits of this drug education study derive both from the knowledge gained by trialling an optimum combination of innovative, harm reduction approaches with a large, student sample, and the resultant product. The research will provide better understanding of what benefits can be achieved by harm reduction education. It will also produce an intervention, dealing with both licit and illicit drug use that has been thoroughly evaluated in terms of its efficacy, and informed by teacher and student feedback. This makes available to schools a comprehensive drug education package with prevention characteristics and useability that are well understood.

**Trial registration:**

Australia and New Zealand Clinical Trials Register (ANZCTR): ACTRN12612000079842

## Background

The health and social costs associated with alcohol and other drug (AOD) use are considerable and fall most heavily on young people [1-3]. This in itself is an argument for early AOD prevention programs. School drug education offers the potential to prevent problems by equipping young people with the knowledge and skills to make responsible decisions about AOD use, and it has near universal reach in developed countries where the great majority of young people attend secondary school [4]. However, historical approaches to school drug education have not been particularly successful at reducing AOD use [5-7]. This then poses the question as to whether effectiveness should be measured by abstinence or reduced use, or whether harm reduction is a more realistic and useful measure. Harm reduction programs offer greater promise of achieving worthwhile benefit because they have the flexibility to select strategies on the basis of evidence of effect. Within this model abstinence or reduced use strategies may be chosen if there is evidence that they reduce harm, but they are not goals in their own right [8].

The School Health and Alcohol Harm Reduction Project (SHAHRP) demonstrated the effectiveness of a skills based, harm reduction intervention. Students who received the SHAHRP program experienced 22.9% less alcohol-related harm than their control peers [9]. A more recent study of computerised harm reduction prevention similarly reported that alcohol consumption, risky drinking and alcohol-related harms increased to a lesser extent among female intervention students, although there was no program effect among male students [10]. A related study that targeted cannabis, as well as alcohol, found that weekly alcohol consumption of intervention students decreased, while that of their control peers increased. The frequency of drinking to excess also increased to a lesser extent among the intervention students [11].

Drug education has developed considerably in Australia over the past decade. However, evidence-based practice tends to be best reflected in demonstration programs that focus on a single drug type, such as alcohol [9,12]. The most recent findings have not been brought together in a mass drug education program that targets all forms of drug use and can be readily accommodated within a secondary school health curriculum. Past classroom-based programs have not well exploited the important influence that parents have on their children in terms of AOD choices and the likely benefits of increased communication on this issue [13]. Finally, while most Australian school drug education programs are grounded in the research literature and principles of effective practice there has been insufficient attention to the pedagogy required to deliver effective classroom lessons [14]. Drug education is most effective when inclusive, interactive teaching strategies actively engage students in the learning process [14,15]. However, reviews of drug education program implementation consistently identify a breakdown in fidelity when learning tasks are interactive [16-18].

This research study seeks to extend earlier Australian harm reduction education research by investigating the prevention effects of a single program for both licit and illicit drugs. The size and nature of the intervention have been tailored to facilitate incorporation within an already crowded school curriculum. It draws on the recent literature as to the common elements in effective school drug education programs [19-22]. It seeks to incorporate the social influence of parents through structured home activities that complement the classroom lessons. It emphasises the use of appropriate pedagogy through two days of training, where participatory delivery of each lesson is modelled to ensure teachers are equipped to teach the program as intended. All these elements have been trialled and refined during the course of a two year pilot program that was undertaken in four Victorian government secondary schools (three intervention and one control) [23].

### Conceptual underpinnings

The intervention at the heart of this study is grounded in social learning theory, which posits that human learning occurs in a social context [24]. In this model, drug use is socially learned through modelling, imitation and reinforcement, and influenced by an individual's cognitions, attitudes, and beliefs. The corollary is that drug education can use the same learning processes to equip students with the skills to recognise these influences and develop a repertoire of counter behaviours. Social learning theory underpins all of the most effective school drug education programs, and a number of researchers have indicated that it should be the model of choice in any prevention program [7,19,25].

The intervention also draws on two other theoretical models, poststructuralist subjectivity and cognitive dissonance. Poststructuralist subjectivity theory provides a way of understanding how students' self concepts, and hence their approach to drug use, can change. Cognitive dissonance theory provides a way of understanding how students resolve conflicting ideas on drug use.

Poststructuralist subjectivity theory refers to the ways in which the social world is involved in shaping an individuals' sense of self [26,27]. It posits that cultural norms and expectations shape the individual's sense of who they can or should be, and identifies the importance of a 'sense of belonging' to identity formation [28]. In this process of subjectification, identity is continuously under construction, maintenance and re-construction, and hence open to change, particularly change that is social and collective in nature. Thus participatory and collective learning methods become the vehicle for the creation of new norms and possibilities in the peer group [14,15,29].

Festinger's theory of cognitive dissonance posits that contradictory cognitions, or cognitive dissonance, cause mental discomfort [30]. This serves as a driving force that compels a person to adopt new thoughts or beliefs, or to modify existing beliefs, so as to reduce the amount of dissonance between cognitions. The education intervention used in this study does not tell students what they should think or how they should behave in terms of drug use. Rather, it provides a social learning process whereby the students reach their own conclusions through exploration of drug use issues. By guiding students through an interactive discovery process that involves articulation of responsible drug use behaviour their ownership of that behaviour is reinforced and they are less likely to behave in a contrary manner.

### Aims and hypothesis

The aim of this study is to develop and assess the effectiveness of a comprehensive, evidence-based, harm reduction focused school drug education program for year eight and nine students by undertaking a cluster randomised trial with 21 secondary schools in the Victorian state of Australia. The specific hypothesis is that while the intervention students may not be any less likely to take up use of alcohol, tobacco and illicit drugs they will be more likely to consume in a less risky manner and experience less harms associated with use.

## Methods/design

### Study design

Twenty one Victorian government high schools have been recruited to the study. The schools were then allocated to four strata: six schools to metro location, high SES; three schools to rural location, high SES; six schools to metro location, low SES; six schools to rural location, low SES. This approximated the proportion of Victorian secondary schools in each category. Within each strata the schools were then randomly allocated to intervention or control conditions on a two to one proportion to allow more precise statements about the effects of the intervention [31]. Random allocation and allocation concealment were achieved by one member of the research team writing the names of each school on identical paper chits which were then folded to conceal the name. The same researcher also created seven chits with the word control and 14 with the word intervention. These were similarly folded to conceal the words. The chits with the school name and those designating allocation were placed in separate containers. A different member of the team then simultaneously drew out a chit with the name of a school and a chit designating either control or intervention allocation.

The study will follow a cohort of students from the start of year eight, when most are 13 years old, to the end of year ten, when most would have turned 16. Pre intervention, baseline testing will occur at the beginning of year eight (Mar/Apr). The first phase of the drug education intervention will occur in the middle of that year (Jul/Sep). Post 1 testing will occur at the end of the same year (Nov/Dec), approximately 8 months subsequent to baseline. The second phase of the drug education intervention for the students, now in year nine, will occur in the middle of the second year of the study. Post 2 testing will occur at the end of the second year. In the third year, when the students are in year ten, no further drug education lessons will be provided as part of this study, but schools will continue with their usual year ten drug education curriculum. Post 3 testing will occur at the end of the year. Throughout the study control students will receive the drug education normally provided by their school. The research sequence is illustrated in Figure 1. Fidelity data will be collected from all participating teachers on a lesson by lesson basis via an on-line survey. In addition, focus groups/interviews will be used to collect qualitative information about the relevance and suitability of lesson materials from students and teachers in a sample of five of the 14 intervention schools following delivery of both the year eight and the year nine program. The student focus groups will be one hour in duration with a roughly even mix of six to eight males and females. Teacher interviews will also be one hour long with either individuals, or small groups of two to three respondents.

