### Statistical analysis

Multi-level modelling can best accommodate hierarchically structured data and will be used in this analysis, adjusting for any baseline differences between the intervention and control groups [42,43]. The hierarchy in this longitudinal multi-level dataset comprises level 1 units (occasions of repeated measurement), nested within the level 2 units (the individual student), nested within the level 3 units (the school). Stata version 10.0 will be used for model fitting, with a three-level mixed regression model fitted to the data to account for the repeated observations [44]. If necessary, the knowledge, consumption and harm scales will be log-transformed to satisfy the assumption of normality. If normality cannot be achieved by log-transformation, non-parametric procedures will be used for analysis. All analyses will be conducted on an Intent-to-Treat basis. Complete-case analysis (CCA) will be complemented with multiple imputation analysis (MIA) to account for missing data.

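### The chit draw is described without a stratum step although allocation is said to be 2:1 within four strata, and the stated model does not carry the strata

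*Protocol article*

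**What the plan says.** The Study design section of the protocol article puts the 21 schools into four strata: metropolitan high SES (6), rural high SES (3), metropolitan low SES (6) and rural low SES (6). It then states the rule: "Within each strata the schools were then randomly allocated to intervention or control conditions on a two to one proportion".

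The mechanism follows. One team member wrote each school's name on a folded chit. "The same researcher also created seven chits with the word control and 14 with the word intervention". "The chits with the school name and those designating allocation were placed in separate containers". A second team member then "simultaneously drew out a chit with the name of a school and a chit designating either control or intervention allocation". Nothing here says that the chits were sorted by stratum, that each stratum had its own containers, or that the draw went stratum by stratum. Nothing says that all 21 names went into one pool either.

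The Statistical analysis section gives "a three-level mixed regression model fitted to the data to account for the repeated observations", with occasion, student and school as the levels. The only adjustment it mentions is for differences between the arms at baseline. Location, SES and the strata are not named.

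**The concern.** The rule and the mechanism should describe the same procedure. Taken literally, the mechanism is a single draw of 21 names against 14 intervention and 7 control chits. That fixes the overall ratio and nothing else, so balance on location and SES would be left to chance.

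The analysis has a related weakness. Adjustment that is triggered by observed baseline differences tends to pass over the factors that stratification has already balanced. Stratification takes between-stratum variation out of the true variance of the arm comparison. A model without the strata leaves that variation in the school-level residual, so its standard error is usually too large. With only 21 schools, of which 7 are controls, avoidable imprecision at school level is worth removing.

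**Working it through.** **Inputs from the documents.** Strata of 6, 3, 6 and 6 schools; a 2:1 ratio; 7 control and 14 intervention chits (all Study design); 1746 students in 21 schools (Sample).

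**Step 1: reproduce the plan's totals under a stratified draw.** One third of each stratum goes to control:

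- control: 6/3 + 3/3 + 6/3 + 6/3 = 2 + 1 + 2 + 2 = 7
- intervention: 4 + 2 + 4 + 4 = 14

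These are the stated chit counts, so the counts do not conflict with stratification. A draw by stratum would need chit sets of 2 control and 4 intervention for each six-school stratum, and 1 and 2 for the three-school stratum. Two to one then holds in every stratum with certainty.

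**Step 2: the same totals under one pooled draw.** There are C(21,7) = 116,280 equally likely choices of control schools.

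- Exactly 2:1 in all four strata: C(6,2) × C(3,1) × C(6,2) × C(6,2) = 15 × 3 × 15 × 15 = 10,125, and 10,125/116,280 = 8.7%.
- No control school in the rural high-SES stratum: C(18,7)/C(21,7) = 31,824/116,280 = 27.4%.
- At least one stratum without a control school, by inclusion–exclusion: [31,824 + 3 × C(15,7) − 3 × C(12,7) − 3 × C(9,7)]/116,280 = [31,824 + 19,305 − 2,376 − 108]/116,280 = 48,645/116,280 = 41.8%.

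A pooled draw would therefore deliver the stated allocation only by luck.

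**Step 3: what the strata might be worth in the model.** The documents give neither an ICC nor the share of between-school variance that the strata explain. Both are assumptions here. Students per school at the end of the study are taken as 1746/21 = 83.1, times 0.85³ = 0.614, which is about 51. The 15% annual loss is the figure the article quotes for the earlier SHAHRP study; applying it here is also an assumption.

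The between-school share of the variance of a school mean is ICC / [ICC + (1 − ICC)/51]. If the strata explain a fraction *f* of the between-school variance, the ratio of interval widths (with strata to without) is √(1 − *f* × share) × t₁₆/t₁₉. The t ratio is 2.120/2.093 = 1.013: 21 schools less 2 leaves 19 df, and less 3 more leaves 16.

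| ICC (assumed) | Share | *f* (assumed) | Width ratio | Change in width |
|---|---|---|---|---|
| any | – | 0 | 1.013 | about 1% wider |
| 0.02 | 0.51 | 0.10 | √0.949 × 1.013 = 0.987 | about 1% narrower |
| 0.01 | 0.34 | 0.30 | √0.898 × 1.013 = 0.960 | about 4% narrower |
| 0.02 | 0.51 | 0.30 | √0.847 × 1.013 = 0.932 | about 7% narrower |
| 0.05 | 0.73 | 0.30 | √0.781 × 1.013 = 0.895 | about 10% narrower |

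This treats the comparison as one of school means and ignores any stratum differences that adjustment for baseline outcome would already absorb, so the gains may be smaller in the full model.

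**The case against.** A reader might infer that the article contradicts itself and that the schools were in fact drawn from one pool. The text does not support that. It states within-stratum allocation outright and never mentions a single pool. The chit paragraph follows directly and can be read as the mechanics of that step, and 7 and 14 are exactly the summed stratum quotas. The 8.7% is conditional on a pooled draw; it is not evidence that one took place. All of this stands. What remains is that the totals fit both readings and so cannot settle the matter. The Sample section does not settle it either: it classifies schools by other groupings (4, 10 and 7 by location; 6, 10 and 5 by SES) and gives no school counts by stratum and arm.

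A reader might also infer that the model excludes the strata. It does not say so. Listing occasion, student and school as levels leaves room for fixed effects, and a condensed article may leave its covariate list to a fuller document. That also stands, and it makes the analysis point secondary. It is still worth raising because the article does state an adjustment rule, and that rule looks to observed differences between arms. Followed as written, it would tend to omit factors balanced by design.

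Finally, the precision gain rests on assumed inputs and could be nil. That is correct, and it is why a range is shown.

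**Conclusion.** The point holds as an unclear record of randomisation with a consequence for the analysis. It does not establish a contradiction or a faulty allocation. The rule says stratified, and the mechanism as printed has no stratum step. Which was done decides whether balance on location and SES is a property of the design (certain under a draw by stratum, 8.7% for the full 2:1 pattern under a pooled draw).

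If randomisation was stratified as stated, the strata belong in the outcome models. The effect on interval width runs from about 1% wider to about 10% narrower over the assumed values shown. This is a cheap improvement; it gives no reason to doubt the trial's validity.

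**What to change.** 1. Rewrite the allocation paragraph to say whether the draw was made separately in each stratum and, if so, with which chits. Give the number of schools by stratum and arm. Allocation is complete, so this corrects the record and changes nothing in the design.
2. Given the stated stratified randomisation, enter the four strata as fixed effects (three terms) in the outcome models, fixed in advance and regardless of any observed baseline difference.
3. If the draw proves to have been a single pool, describe the allocation as unstratified. The design then no longer requires the strata in the model, and using location and SES becomes an ordinary choice of covariates, to be fixed before outcomes are analysed.

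The cost is one paragraph and 3 of about 19 school-level degrees of freedom, at worst an interval about 1% wider.

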**Figure 1 F1:**
[figure not shown]
**Schematic illustration of the research design**.

### Sample size calculation

The ability to detect small changes in substance use, knowledge, attitudes and harms experienced is central to this study. The primary outcome is a change in alcohol consumption patterns and associated harm, and accordingly sample size estimations are based on detecting a small effect size of .15 in relation to these measures. This effect size was chosen on the basis of previous school drug education studies [9,32].

The target sample size has been estimated using G*Power v.3.1.3 software where α = 0.05 and 1-β error probability = 0.95 [33]. Assuming simple random sampling, a total sample size of 364 is required at the end of the study. However, there is a design effect due to the loss of effectiveness created by cluster sampling. The design effect for the SHAHRP study, which took into consideration the effect of clustering by school and a 15% annual rate of student attrition, was calculated to be 1.48. Using this correction, a total sample size of at least 539 is required to test the effectiveness of the intervention.

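### The 364 students for 95% power at an unlabelled effect size of .15 most likely come from Cohen's f (d = 0.30) in a test that does not fit the trial's 2:1, baseline-adjusted design, and the reason given for 2:1 is backwards

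*Protocol article*

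**What the plan says.** The Sample size calculation section defines the target outcome ("The primary outcome is a change in alcohol consumption patterns and associated harm") and says that "sample size estimations are based on detecting a small effect size of .15 in relation to these measures". It then gives the software, significance level and power: "The target sample size has been estimated using G*Power v.3.1.3 software where α = 0.05 and 1-β error probability = 0.95". The result is "Assuming simple random sampling, a total sample size of 364 is required at the end of the study". A design effect borrowed from an earlier school alcohol study, which "took into consideration the effect of clustering by school and a 15% annual rate of student attrition, was calculated to be 1.48", turns this into "a total sample size of at least 539 is required to test the effectiveness of the intervention". The section states no metric for .15, no statistical test, no number of measurements, no correlation between measurements and no allocation ratio.

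Elsewhere the article describes:
- 14 intervention and 7 control schools, allocated "on a two to one proportion to allow more precise statements about the effects of the intervention" (Study design);
- four surveys, the first before any lessons are taught (Study design);
- 1746 enrolled students, 1230 intervention and 516 control (Sample);
- a three-level mixed model adjusting for baseline differences (Statistical analysis).

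**The concern.** In a two-arm trial, many readers will take an effect size of .15 called small as a standardised mean difference. On that reading 364 is too few by a factor of six to seven. The figure does appear under a different metric and a particular test, but that test assumes equal arms and averages in a survey at which no effect can yet exist. The reader therefore cannot tell which effect carries the 95% power. If the trial finds no difference, the result could be taken as 95%-powered evidence against a standardised difference of 0.15, which the printed calculation does not support.

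The Study design section adds to this by presenting unequal allocation as a gain in precision.

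**Working it through.** **Inputs from the article.** Effect size 0.15; alpha 0.05 (taken as two-sided); power 0.95; N = 364; design effect 1.48; 14:7 schools; 1230:516 students; four surveys. **Assumed, not in the article:** a correlation of 0.5 between surveys.

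**1. Reproducing 364.** In the repeated-measures ANOVA between-factors test with two equal groups and m surveys, the noncentrality is λ = N·f²·m / (1 + (m − 1)ρ), with 1 and N − 2 degrees of freedom. Put f = 0.15, m = 4, ρ = 0.5:
- N = 364: λ = 364 × 0.0225 × 4 / 2.5 = 13.10, power 0.9506.
- N = 362: λ = 13.03, power 0.9495.

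So 364 is the smallest even total reaching 95%, and 364 × 1.48 = 538.7, which rounds to 539. In two equal groups d = 2f, so f = 0.15 means d = 0.30.

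**2. Other routes tried at alpha 0.05 and power 0.95.**

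| Test | Total N |
|---|---|
| Two-sample comparison, d = 0.15, 1:1 | 2314 |
| Two-sample comparison, d = 0.15, 2:1 | 2601 |
| One-way ANOVA, f = 0.15 | 580 |
| Between factors, f = 0.15, 2 surveys, ρ = 0.5 | 436 |
| Between factors, f = 0.15, 3 surveys, ρ = 0.5 | 388 |
| Group-by-time interaction, f = 0.15, 4 surveys, ρ = 0.5 | 98 |
| Between factors, d = 0.15 (f = 0.075), 4 surveys, ρ = 0.5 | 1446 |

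**3. Fit of that test to the trial.** The variance of a four-survey mean at ρ = 0.5 is (1 + 3 × 0.5)/4 = 0.625. With 364 students split 2:1 (242.7 and 121.3) and d = 0.30, λ = 0.09 / [0.625 × (1/242.7 + 1/121.3)] ≈ 11.65, giving 92.6% power rather than 95%. One of the four surveys averaged is the pre-intervention baseline. The stated outcome is a change, and the planned model adjusts for baseline.

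**4. If .15 is a standardised mean difference, power at N = 364.**
- One survey: 30% (1:1) or 27% (2:1).
- Four-survey mean, ρ = 0.5: 44% (1:1) or 40% (2:1).

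**5. Power with the students enrolled.** Divide each arm by 1.48 (831.1 and 348.6) and use λ = d² / [v(1/831.1 + 1/348.6)], where v is the outcome variance under each analysis at ρ = 0.5:

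| Analysis | v | Power, d = 0.15 | Power, d = 0.30 |
|---|---|---|---|
| Final survey, unadjusted | 1 | 65% | 99.7% |
| Final survey, baseline-adjusted | 1 − 0.25 = 0.75 | 77% | >99% |
| Four-survey mean | 0.625 | 84% | >99% |
| Mean of three post surveys, baseline-adjusted | 2/3 − 0.25 = 0.417 | 95% | >99% |

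**6. Allocation.** Variance of the between-arm comparison relative to an even split:
- Schools: (1/14 + 1/7) / (2/10.5) = 1.125, an increase of 12.5%.
- Students: (1/1230 + 1/516) / (4/1746) = 1.20, an increase of about 20%.

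**The case against.** The strongest reply is that nothing is miscalculated. If .15 is Cohen's f, 364 is right for its own test and 539 follows. The article never calls .15 a standardised mean difference, and a condensed article may leave the test's settings to the full protocol. This stands in part: a reader might infer that the authors made an arithmetic error with d = 0.15, but the text does not name the metric, so that cannot be shown.

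A reader might also infer that 364 can arise in only one way. It cannot be put so strongly. The match needs a correlation of 0.5 that the article does not give, and less usual settings land on or very near the same figure: f = 0.15 over three surveys at a correlation of about 0.44, over two surveys at about 0.25, or an f = 0.075 interaction over four surveys at about 0.52. The exact match with four surveys and 0.5 makes the described route the most likely one, not a certain one. The averaging over baseline and the equal groups are therefore inferences about the calculation.

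Finally, enrolment is more than three times the target (1746 against 539). On the article's own design effect the trial is well powered for d = 0.30, and the 2:1 shortfall at 364 has no practical effect at 1746. This stands.

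What survives is that the article prints an effect size, a power and a sample size that cannot be read together without an unstated metric, and the likely calculation is not one for the trial described. The allocation sentence rests on a cited source not available here, but the variance ratio for the between-arm comparison does not depend on it.

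**Conclusion.** The sample size statement needs correcting. As printed, 364 (or 539) does not support 95% power for a standardised difference of 0.15: that would take 2314 students at 1:1 or 2601 at 2:1 before the design effect. On the f reading, the figure is for d = 0.30 in equal arms, and at 2:1 the same test gives 92.6%.

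A reader might go further and conclude that the trial as enrolled is badly underpowered. The article does not support that. With 1746 students and the 1.48 design effect, power for d = 0.15 lies between 65% and 95% according to the analysis, and is over 99% for d = 0.30. Much lower values, such as 41% down to 21% for d = 0.15, require an unadjusted single survey, assumed intraclass correlations of 0.01 to 0.05, and 15% yearly loss applied again although the 1.48 is said to include it. Further attrition or a larger intraclass correlation would lower power, but both are assumptions.

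The allocation claim is wrong for the between-arm effect whatever the metric: 2:1 costs about 12.5% in variance at school level and about 20% at student level. Only the intervention arm's own estimate becomes more precise.

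**What to change.** In Sample size calculation:
- State that .15 is Cohen's f, equivalent to d = 0.30 in equal groups, or recompute for d = 0.15.
- Name the test, the number of surveys and the correlation assumed.
- Replace the 95% claim with the power, or the minimum detectable difference, of the actual 14:7 schools and 1230:516 students under the planned baseline-adjusted model, with the intraclass correlation and attrition assumptions shown.

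In Study design, delete the claim that 2:1 allows more precise statements about the intervention effect. If another reason for 2:1 exists, give it together with its efficiency cost.

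The cost is one rewritten paragraph and one sentence. No extra students are needed. The downside is a less favourable stated power if the target is d = 0.15.

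### The borrowed factor of 1.48 cannot cover both clustering and 15% yearly attrition over this trial's follow-up, so the stated minimum of 539 falls short of the plan's own 364 at the end of the study

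*Protocol article*

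**What the plan says.** The protocol article, under Sample size calculation, bases the calculation on a standardised effect of 0.15 for alcohol consumption and harm, "where α = 0.05 and 1-β error probability = 0.95". The starting number is an end-of-study number: "Assuming simple random sampling, a total sample size of 364 is required at the end of the study". The article then notes that cluster sampling costs precision and takes a design effect from SHAHRP, the earlier school alcohol harm reduction study, "which took into consideration the effect of clustering by school and a 15% annual rate of student attrition, was calculated to be 1.48". It concludes: "Using this correction, a total sample size of at least 539 is required to test the effectiveness of the intervention".

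Under Study design, baseline testing is in March/April of year eight. Post 1 is about 8 months later, and Post 2 and Post 3 fall at the end of years nine and ten. The abstract describes "21 Victorian secondary schools over a period of three years". The Sample section reports 1746 consenting students, 1230 intervention and 516 control. The article gives no intracluster correlation (ICC), and neither the cluster size nor the follow-up length behind the 1.48.

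**The concern.** One multiplier is asked to do two jobs: to compensate for students lost before the last survey, and to compensate for the similarity of students within a school. Each job needs a factor of at least 1, so the product cannot be smaller than either factor. If yearly losses of 15% over this trial's follow-up already need more than 1.48, the combined factor is too small whatever the ICC.

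Two things are at stake. The article's stated minimum would not deliver its own end-of-study requirement. And the comparison that a reader will make, 1746 enrolled against 539 required, suggests a surplus of 1746/539 = 3.2 times. The true margin depends on an ICC that the article does not state, and this matters for interpreting a null result in a trial of 21 schools designed around a small effect.

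**Working it through.** **Inputs from the article.** 364 needed at the end of the study; factor 1.48; attrition 15% a year; 21 schools; 1746 enrolled. Follow-up from baseline to Post 3 is 8 + 24 = 32 months, or 2.67 years; three full years is used as the other end of the range. The 364 is taken as given. It can be reproduced as a repeated-measures between-groups F test with f = 0.15, two equal groups, four occasions and an assumed correlation of 0.5, but nothing below depends on that.

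**The plan's figure.** 364 × 1.48 = 538.7, rounded up to 539. It reproduces.

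**Attrition alone.** Retention is 0.85^t, and the factor needed is 1/0.85^t.

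| Follow-up t (years) | Retention | Factor for attrition alone | 539 recruits leave | Recruits needed to keep 364, no clustering | Left in 1.48 for clustering (1.48 × retention) |
|---|---|---|---|---|---|
| 2 | 0.7225 | 1.38 | 389 | 504 | 1.07 |
| 2.67 | 0.648 | 1.54 | 349 | 562 | 0.96 |
| 3 | 0.614 | 1.63 | 331 | 593 | 0.91 |

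Attrition alone uses up 1.48 at ln(1.48)/−ln(0.85) = 2.41 years, before Post 3. If losses are added rather than compounded, the result is worse: 40% lost at 2.67 years leaves 323, and 45% lost at 3 years leaves 296.

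**If 539 is an end-of-study number.** Treating 1.48 as all clustering, recruitment would have to be 538.7/0.648 = 831 (2.67 years) or 538.7/0.614 = 878 (3 years). The article makes no such further allowance.

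**The two factors separated.** With the number of schools K fixed at 21, students retained per school are m = n/K, where n is the total retained. The requirement is n = 364 × [1 + (n/21 − 1) × ICC], which solves to

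n = 364 × (1 − ICC) / (1 − 364 × ICC/21).

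Recruits are n/0.614 (three-year retention). The ICC values are assumed, because the article gives none; equal clusters are also assumed.

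| Assumed ICC | n retained | Recruits needed |
|---|---|---|
| 0.01 | 360.4/0.827 = 436 | about 710 |
| 0.02 | 356.7/0.653 = 546 | about 889 |
| 0.03 | 353.1/0.480 = 736 | about 1198 |
| 0.05 | 345.8/0.133 = 2594 | about 4223 |

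The steep rise at 0.05 comes from the fixed number of schools: extra students per school add less and less.

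**The trial as enrolled.** 1746 × 0.648 = 1132, or 1746 × 0.614 = 1072. Divided by 364, this allows a clustering design effect of 3.11 or 2.95. At 1072/21 = 51 students per school, the largest ICC that still meets 364 is (2.95 − 1)/(51 − 1) = 0.039; at 1132/21 = 54 per school it is about 0.040.

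**The case against.** Four replies deserve weight.

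1. *539 may not be a recruitment number.* The sentence does not say so, it follows directly on an end-of-study 364, and a design effect that allows for attrition could mean one computed at the cluster size left after attrition. On that reading the shortfall from 539 to 349 or 331 does not arise. This stands as an ambiguity, but it does not rescue the target, which would then contain no allowance for the 15% yearly loss. The plainer reading, that 1.48 already includes attrition, makes 539 the number to recruit.

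2. *The 1.48 and the 15% belong to the earlier study.* This stands. With two yearly losses, 1.48 leaves a possible 1.07 for clustering. A reader might infer that the earlier study's factor was miscalculated; the article does not support that, because it gives neither that study's follow-up nor its cluster size. For the same reason, no ICC can be recovered by solving 1.48 backwards with this trial's school sizes. What fails is the transfer to a follow-up of 2.67 to 3 years.

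3. *The trial enrolled far more than 539.* This stands and limits the consequence. A reader might infer that the trial is underpowered; the figures do not show that.

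4. *A condensed article leaves such detail to the full protocol.* That excuses the absence of an ICC and a power table. It does not excuse a stated minimum that conflicts with the attrition rate and schedule in the same article.

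**Conclusion.** The point holds. On the plain reading, 1.48 is smaller than the factor that attrition alone requires at the article's own 15% a year (1.54 at 2.67 years, 1.63 at three years), and 539 recruits would leave 15 to 33 fewer than the 364 required, before any penalty for clustering. On the alternative reading, the number to recruit is understated by 292 to 339 (831 or 878 against 539), even if 1.48 is all clustering.

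The conclusion rests on attrition running through to Post 3; it would fail only if losses were counted for less than about 2.4 years. It does not rest on any ICC. The restated minima do: they use assumed ICCs, equal clusters and the plan's 364 as it stands.

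Severity is moderate. The stated minimum is wrong, but enrolment is well above it, and the plan's 364 is met up to an ICC of about 0.039. The apparent 3.2-fold surplus is what does not survive: it becomes about 2.0 (1746/889) at an ICC of 0.02 and 1.5 (1746/1198) at 0.03, and it vanishes above about 0.039.

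**What to change.** Replace the single 1.48 by two explicit factors:

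- a clustering factor, 1 + (m − 1) × ICC, with m the students retained per school in this trial and the number of schools fixed at 21;
- division by expected retention at Post 3, between 0.85^2.67 = 0.648 and 0.85^3 = 0.614.

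State the ICC range and its source, restate the minimum, and say whether it is a recruitment or an end-of-study number. At 61.4% retention the recruitment minimum would be about 710, 889, 1198 or 4223 for ICCs of 0.01, 0.02, 0.03 or 0.05, which are illustrative until a source is given. Then report power at the 1746 enrolled over the same range.

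The cost is two sentences and a small table. No new recruitment is implied, and the only downside is a less favourable stated minimum.
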